## Abstract

**Background:**

Haemorrhoids are common and frequently occurring diseases in the clinical setting, and severe haemorrhoids require surgical treatment. There are various surgical methods to treat haemorrhoids, but each has advantages and disadvantages. In recent years, ultrasonic scalpels have been used in haemorrhoid surgery and have achieved good results. Ultrasonic scalpel haemorrhoidectomy is safer and more effective in the surgical treatment of grade III and IV haemorrhoids, with less intraoperative bleeding, less postoperative pain, and fewer complications than diathermic therapy, electrosurgical haemorrhoidectomy, PROXIMATE® PPH haemorrhoidal circular stapler haemorrhoidopexy (PPH), and traditional haemorrhoidectomy. In previous reports, the majority of ultrasonic scalpel haemorrhoidectomies were performed as open procedures, with only the body of the haemorrhoid removed with the ultrasonic scalpel and the wound left open for drainage and natural healing. However, we performed a preliminary experiment with 12 patients who underwent open ultrasonic scalpel haemorrhoidectomy in the early stage. The results showed that 8 patients had different degrees of postoperative bleeding, and 4 of them required a second haemostatic surgery under anaesthesia. Therefore, we modified the open ultrasonic scalpel haemorrhoidectomy procedure by removing the mucosa of the internal haemorrhoid and closing the base of the incision with figure-eight penetrating sutures and designed this study protocol to evaluate its clinical efficacy and safety.

**Methods:**

A randomised single-blind parallel-controlled trial is proposed for this project, and patients who meet the inclusion criteria will be divided into a test group and a control group, with 39 patients in each group. The experimental group will be treated with modified ultrasonic scalpel haemorrhoidectomy, and the control group will be treated with the Milligan-Morgan operation. The effectiveness of modified ultrasonic scalpel haemorrhoidectomy for haemorrhoids will be objectively evaluated, including the incision healing time and the time for patients to return to normal activities, postoperative complications, evaluations of anal function 3 months and 6 months after surgery, an evaluation of quality of life 6 months after surgery, and an evaluation of the patient satisfaction rate 6 months after surgery. The safety assessment will consider all adverse and serious adverse events associated with the study treatment.

**Discussion:**

The study was approved by the ethics committee. The first patient was registered on July 1 2021. The purpose of this trial will be to evaluate the clinical efficacy and safety of the modified ultrasonic scalpel haemorrhoidectomy procedure for the treatment of mixed haemorrhoids and to provide an evidence base for the clinical promotion and application of the procedure. A limitation of this study is that only the patients will be single-blinded because the researchers and the patients cannot be blinded at the same time, which may produce certain bias in the results. In addition, the sample size of this study will be small, and the test results will only represent the findings from this clinical trial. In later stages, the sample size needs to be further expanded to improve the level of evidence. Despite its limitations, we hope the present study will help provide a more optimised surgical approach in the selection of haemorrhoid surgery.

**Trial registration:**

Chinese Clinical Trial Registry (Registration ID: ChiCTR2100047229). Registered on June 11, 2021.

## Introduction

### Background and rationale

Haemorrhoids are a common and frequently occurring clinical disease, and the prevalence rate accounts for approximately 40% of the total population. The disease may occur in both men and women and may progressively worsen with age. Nonsurgical treatment does not significantly improve the symptoms of severe haemorrhoids, and they usually have irreversible pathological anatomy and physiological functions; therefore, it is necessary to treat severe haemorrhoids by surgery. At present, the commonly used surgical methods include the Milligan-Morgan operation [1], the PROXIMATE® PPH haemorrhoidal circular stapler haemorrhoidopexy (PPH) [2], and automatic haemorrhoid ligation (RPH) [3]. The Milligan-Morgan operation is a classic operation for the treatment of haemorrhoids; although it can significantly improve some clinical symptoms of patients, this procedure causes greater tissue damage and more bleeding during the operation, and the incidence of complications such as wound edge oedema and pain is higher [3]. Both PPH and RPH have some postoperative complications, such as postoperative haemorrhage and reoperation [4].

With the rapid development of minimally invasive medicine and the continuous improvement of medical instruments, there are an increasing number of studies regarding energy device procedures for haemorrhoidectomy in addition to conventional surgical devices, such as LigaSure™ haemorrhoidectomy [5, 6], ultrasonic scalpel haemorrhoidectomy, laser haemorrhoidectomy [7], and Starion haemorrhoidectomy [8]. As a new surgical equipment in clinical surgery, ultrasonic scalpels were used in clinical surgery in 1992 and are now widely used in various surgical operations. Their working principle is to make the metal cutter head oscillate at a frequency of 55.5 kHz through an ultrasonic frequency generator so that the water molecules in the tissue are vaporised, the hydrogen bonds of proteins are broken, and cells can disintegrate to cut the tissue and coagulate the blood vessels. Ultrasonic scalpels convert electrical energy into mechanical energy without electrical conduction and have high safety. Compared with traditional electric scalpels, ultrasonic scalpels cause the least damage to tissues (causing thermal damage to an area 1–3 mm wide), have less smoke, and do not cause neuromuscular stimulation [9, 10]. In recent years, ultrasonic scalpels have been gradually used in haemorrhoid operations and have shown good results. Some scholars have compared ultrasonic scalpel haemorrhoidectomy with diathermy therapy [11]. Ferguson’s with electrosurgical haemorrhoidectomy (FEH) [12], PPH [13], and traditional haemorrhoidectomy [14, 15]. The results showed that ultrasonic scalpel haemorrhoidectomy was safer and more effective in the surgical treatment of grade III and IV haemorrhoids, with less intraoperative bleeding, less postoperative pain, and fewer complications. Tsunoda A [16] studied transurethral Doppler-guided arterial mucopexy for haemorrhoids removal and ultrasonic scalptor haemorrhoidectomy for third-degree haemorrhoids. The medium-term results demonstrated that US has a faster return to normal activities. Domestic scholars Yuan Xiaoqian et al. [17] applied ultrasonic scalpel haemorrhoidectomy combined with band ligation therapy to treat mixed haemorrhoids, and the results showed that the combination was safe and effective in the treatment of mixed haemorrhoids, with the advantages of a short operation time, less intraoperative bleeding, less postoperative pain, and fast wound healing. Shen Jianyong et al. [18] used a nonligating ultrasound scalpel to treat 57 cases of circular mixed haemorrhoids. The clinical effect was obvious and there were few complications.

### Rationale for study

An ultrasonic scalpel can directly remove haemorrhoids, coagulate blood vessels and tissues, and avoid the disadvantages of massive bleeding during the ligation shedding period and postoperative recurrence after traditional surgery. However, in the preliminary experiment, we found that when only an ultrasonic scalpel was used to remove haemorrhoids without suturing the incision after the operation, the increase in intra-abdominal pressure and pressure in the anal canal due to normal defaecation activities would increase the tissue tension in the anal area. Under repeated stimulation from stool, the solidified tissues would easily crack and bleed, causing incision infection and secondary healing. Therefore, based on the previous literature and clinical studies, we have designed a modified ultrasonic scalpel haemorrhoidectomy procedure and will evaluate its clinical efficacy and safety, aiming to provide evidence for the promotion and application of the procedure in the clinical setting.

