#### Recruitment and trial timeline

Researchers will recruit participants from the inpatient wards of the Department of Integrated Traditional Chinese and Western Medicine. After screening patients who meet the inclusion and exclusion criteria, the researcher will inform the participants of the different treatment methods available for their condition, provide information about the study, and have the participants sign a written informed consent form. A copy will be kept by the participant, and the original will be kept at the hospital. Considering the admission to haemorrhoid surgery in our hospital and the experience of the last 2 years, it is feasible to recruit the calculated patient sample size. Other strategies to increase recruitment include announcing the study on our hospital website and providing information in the waiting room of the hospital.

The participants who meet the criteria will be registered, their baseline data and clinical features will be collected before the operation, and measurements will be taken at each observation time node according to the CRF form after the operation (Table 1). Participants who met the withdrawal criteria shall strictly follow the criteria and provide records. The registration process, the intervention and evaluation schedule, and the study flow chart are shown in Table 1 and Fig. 1.

**Table 1 Tab1:** Schedule of the registration process, the intervention, and evaluations

Measures	Preoperative	Daily in-hospital study visits								Follow-up					
		POD 0	POD 1	POD 2	POD 3	POD 4	POD 5		POD ≥ 6	W 2		W 3	W 4	M 3	M 6
Incision healing time										X	X		X		
Recovery time										X	X		X		
Pain VAS		X	X	X	X	X	X	X		X	X		X		
Urinary retention		X	X	X	X	X	X	X							
Postoperative bleeding		X	X	X	X	X	X	X		X	X		X		
Postoperative oedema		X	X	X	X	X	X	X		X	X		X		
Anal stenosis	X	X	X	X	X	X	X	X		X	X		X	X	X
Cleveland incontinence score	X	X												X	X
SF-36	X	X													X
Satisfaction survey		X													X
Adverese events		X	X	X	X	X	X	X		X	X		X	X	X

*POD* Postoperative day, *W* Week, *M* Month, *VAS* Visual analogue score, *SF36* 36-Item short form health survey

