### Intervention description

#### The treatment group

The external haemorrhoids in the mother haemorrhoid area at points 3, 7, and 11 will be removed by an ultrasonic scalpel in a V-shape;The internal haemorrhoids will be clamped with forceps to be removed, the superior haemorrhoid artery will be ligated with No. 0 mousse thread “8”, 1 ml of Xiaozhilin will be injected under the ligation proximal sticking mould, and then the haemorrhoid will be removed slowly with an ultrasonic scalpel along the clamp mark at the base;The carbonisation (fixation) range of the incision will be checked, the free carbonised tissue will be removed at the incision, a needle will be inserted at the edge of the solidified tissue to suture the incision with the figure of “8” slightly above the tooth line, and then the incision epithelium will be sutured near the tooth line with the modified “8” suture method. When there is no obvious bleeding from the wound, the operation will be considered complete.

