#### Secondary outcome measures

Postoperative complications: pain: A visual analogue scale (VAS) will be used in the two groups to observe the patients’ pain 4 h, 8 h, and 24 h after the operation and the pain from defecation for 7 consecutive days after the operation. Urinary retention will be assessed by the “with” and “without” method. Postoperative bleeding will be assessed as follows: 0 points: no bleeding; 1 point: blood on the paper; 2 points: drops of blood; 3 points: ejection of blood; and 4 points: massive bleeding that requires surgery to stop the bleeding. Postoperative oedema will be assessed as follows: 0 points: no oedema; 1 point: oedema in 1/4 of the anal margin incision; 2 points: oedema in 1/2 of the anal margin incision; 3 points: oedema in 3/4 of the anal margin incision; and 4 points: oedema around the perianal incision. Anal stenosis will be assessed by the “with” and “without” method.

Anal function evaluations 3 months and 6 months after operation: Anal function evaluation will be assessed by the CCF-FI as follows: (1) normal continence: the anus controls stool, and the passage of intestinal fluid and intestinal gas is normal; (2) partial anal incontinence: the anus cannot control intestinal fluid, intestinal gas, or loose stools; there is soiling of the underwear; or the anus has a sense of dampness; and (3) complete incontinence: the anus cannot control the passage of stool.

Evaluation of quality of life half a year after the operation: The simple SF-36 quality-of-life questionnaire (homemade) will be used to evaluate quality of life.

Evaluation of patient satisfaction rate half a year after the operation: The self-designed patient satisfaction questionnaire will be used, which is divided into very satisfied, satisfied, general, and no opinion, and calculates the percentages of the 4 levels.

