## Discussion

There are many surgical methods for haemorrhoids, but each has its own advantages and disadvantages. Therefore, it is particularly necessary to explore a surgical method that not only does not damage anal sphincter function but can also restore the normal shape of the anus.

The choice of surgical instruments for mixed haemorrhoids should not only take into account the different symptoms and morphological characteristics of patients with mixed haemorrhoid lesions but also local related haemodynamic changes, microcirculation control disorders, and haemorheological pathophysiological changes; the concept of “minimally invasive” should be used as much as possible to achieve a good therapeutic effect and protect the fine functions of the anus, such as defecation control. The metal head of the ultrasonic scalpel is sharp and conducive to fine anatomy and is of great value in the operation of mixed haemorrhoids. Ultrasonic scalpel haemorrhoidectomy was reported to be applied in the clinic by Jane [22] and other investigators in 2001, and research has shown that ultrasonic scalpel haemorrhoidectomy can reduce the pain and postoperative bleeding of patients. Mushaya [23] et al. conducted a meta-analysis of the comparison between ultrasonic haemorrhoidectomy and traditional haemorrhoidectomy, and the results showed that the ultrasonic scalpel group had lower pain scores, a lower complication rate, and a faster recovery than the traditional surgery group. Research by Ravi Kumar [24] et al. showed that compared with the Milligan-Morgan operation, ultrasonic haemorrhoidectomy resulted in less blood loss (19.4 and 6.1 ml, respectively). Compared with the Milligan-Morgan method group, the ultrasonic scalpel group had lower VAS pain scores on the first day and the first and the second week after the operation. There were more complications, such as postoperative bleeding and urinary retention, in the Milligan-Morgan group. In a case study of 25 patients (ultrasound scalpel group) conducted by Tariq Ahmed Mala [25], the average operation time was 17.68 ± 2.84 min, and the average operation time of the control group was 28.44 ± 3.69 min. The average blood loss of the ultrasonic scalpel group and the control group was 8.96 ± 2.15 ml and 31.72 ± 3.28 ml, respectively. VAS pain scores on the first day after surgery were 5.92 ± 0.70 in the ultrasonic scalpel group and 8.52 ± 0.84 in the control group. The ultrasound scalpel group had a lower analgesic dose, engaged in walking earlier and returned to normal work faster. In previous research reports, the vast majority of ultrasonic scalpel haemorrhoidectomy procedures were open operations only using an ultrasonic scalpel to remove the haemorrhoids; the wound was left open and drained and healed naturally. Only two studies mentioned that the incision was closed [22, 26]. Another study showed that closing the incision is not beneficial; it is not conducive to drainage of the incision and may actually slow the healing process [27]. Before the start of this study, we conducted a preliminary study: 12 patients with mixed haemorrhoids were treated with open ultrasonic scalpel resection. Unfortunately, 8 of the 12 patients had blood in the stool 5–16 days after the operation, mainly the dripping of blood and jet-like bleeding, and the amount of bleeding was ≥ 5 ml each time. Among them, 4 patients had postoperative bleeding > 50 ml. All 4 patients underwent a second haemostatic operation under anaesthesia. During the operation, the wounds were found to have ulcers and erosions and extensive bleeding after ultrasonic scalpel resection. Upon inquiry into their medical history, the 8 patients with bleeding were found to have no primary underlying diseases (hypertension, heart disease, blood system diseases, etc.) and no history of long-term anticoagulant drug use. The reasons may be as follows: if only the ultrasonic scalpel is used to remove the haemorrhoids without suturing the incision, normal defecation activity after the operation will increase the abdominal pressure and anal pressure, which will increase the tissue tension in the anal area. Under repeated stimulation from stool, the coagulated tissues will easily crack and bleed, causing incision infection and delayed healing. Therefore, we modified the open ultrasonic scalpel haemorrhoidectomy procedure. While removing the internal haemorrhoid mucosa, we sutured the base of the incision with a figure of eight and designed this research plan to evaluate its clinical efficacy and safety.

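### Incision infection, part of the rationale for suturing, is not a solicited complication and rests on adverse-event reporting that may miss it or attribute it differently by arm

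*Protocol article*

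**What the plan says.** The section Rationale for study reports the sponsor's experience with open ultrasonic excision and states that "the solidified tissues would easily crack and bleed, causing incision infection and secondary healing". The Discussion repeats the mechanism: "the coagulated tissues will easily crack and bleed, causing incision infection and delayed healing". The test operation therefore closes the wound; the operator is "to suture the incision with the figure of “8” slightly above the tooth line" and then sutures the epithelium near that line. The section on the control group describes ligation at the base of the haemorrhoid and mentions no closure of the incision.

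The solicited complications are set out under Secondary outcome measures. The list opens with "Postoperative complications: pain: A visual analogue scale (VAS) will be used in the two groups", continues with urinary retention, bleeding (0 to 4) and oedema (0 to 4), and ends with "Anal stenosis will be assessed by the “with” and “without” method". Table 1 has a row for each of these five. The oedema row, for example, begins "Postoperative oedema X X X X X X X" for the hospital stay and has further marks in the early follow-up weeks. There is no row for infection.

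Other provisions bear on the point:
- Objectives: the incidence of adverse and serious adverse events will be compared between the groups.
- Table 1: an adverse-event row runs from the day of surgery to month 6.
- Discharge and follow-up: wound healing and surgical complications are observed at weeks 1 to 4.
- Safety and reporting of serious adverse events: adverse events are defined as events related to treatment and graded by a terminology standard. Collection is described in terms of what participants report of their own accord.
- Randomisation and blinding: operator and observer know the allocation; participants do not.

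**The concern.** The rationale links three wound events: bleeding, incision infection and delayed healing. The plan measures the first on a defined scale and makes the third a primary outcome. The second is left to general adverse-event reporting.

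That route has two weak steps for a local wound event. A mild infection that the participant does not mention need not be recorded. One that is noticed must also be judged related to treatment before it counts, and those making the judgement can know the arm. With no written criterion, both detection and attribution may vary between observers and between arms.

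At stake is how a low infection count may be read. The abstract says the trial is to support wider clinical use of the procedure on efficacy and safety. A low count that was never actively sought says little about either operation.

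**Working it through.** **Step 1. Each event in the rationale against its measurement.**
- Bleeding: graded 0 to 4 under Secondary outcome measures, with a row in Table 1.
- Delayed healing: incision healing time is a primary outcome, with a stated healing criterion and a row in Table 1.
- Incision infection: no item, scale, criterion or row.

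**Step 2. The path by which an infection can reach the data.**
1. It must come to notice. Wounds are inspected in hospital and at weeks 1 to 4, so there is opportunity. The safety section, however, states no active enquiry, only events volunteered by participants.
2. It must be judged related to treatment, because the definition requires it.
3. It is then graded and counted, and incidence is compared by group.

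Participants are blinded, so what they volunteer should depend less on arm. Observation and the causal judgement in step 2 are the parts exposed to knowledge of allocation. The documents give no figure from which the size of either loss could be estimated.

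**Step 3. The denominator.** The Sample size section gives means of 10.50 and 13.40, SDs of 3.46 and 3.66, a two-sided level of 0.05, and 33 per group. The difference is 2.90 and the pooled SD is √((3.46² + 3.66²)/2) = 3.56. A t test then has power 0.894 at 32 per arm and 0.903 at 33, so 33 is the answer at 90% power (inferred, since power is not stated). With 15% loss, 33/0.85 = 38.8, that is 39 per arm and 78 in total, as stated. Adding an infection item changes none of this.

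**Step 4. What a zero count could show.** With 0 events in n, the one-sided 95% upper bound is 1 − 0.05^(1/n).
- n = 39: 1 − 0.05^(1/39) = 7.4%. The two-sided exact limit is 1 − 0.025^(1/39) = 9.0%.
- Trial status says about two thirds of recruitment is complete. One third of 78 is 26, or about 13 per arm: 1 − 0.05^(1/13) = 20.6%.

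These bounds apply only if infection was looked for in every patient counted.

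**Step 5. What a comparison could show.** Fisher's exact test, two-sided 0.05, 39 per arm. The infection rates are assumptions.

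| Assumed rates | Power |
|---|---|
| 2% vs 5% | 0.6% |
| 2% vs 10% | 10% |
| 5% vs 15% | 17% |
| 5% vs 20% | 40% |
| 5% vs 30% | 81% |

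Only a very large difference would be detected. The item is for description.

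**The case against.** The strongest reply is that infection is already covered. The adverse-event row runs to month 6, event incidence is compared between groups, and surgical complications are observed at weeks 1 to 4. A wound infection fits the adverse-event definition if it is judged related to treatment. This stands against any claim that infection cannot be captured. It does not supply a criterion, active enquiry, or freedom from the causal judgement.

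Second, infection is a minor part of the rationale. The problem seen in the 12 preliminary patients was bleeding, in 8 of them, with 4 needing a second operation. The Discussion offers infection only as part of a possible explanation, and no infection is reported in those patients. This limits the weight of the point, but the plan does name the event.

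Third, a reader might infer that the trial ignores a harm its own Discussion raises. The study cited there says of closure that "it is not conducive to drainage of the incision and may actually slow the healing process". That concerns drainage and healing, not infection, and healing time is a primary outcome. Opening of the suture line is named nowhere as a harm; a wound open there would ordinarily fail the healing criterion. The stronger inference is not supported.

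Fourth, an article may leave form-level detail to the full protocol, which is not shown. That is fair for wording on the form. Here, though, the article gives a scoring rule and a schedule row for each complication it solicits, so the selection itself is stated.

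Fifth, late adoption and 39 per arm leave little precision. This is correct and carries into the recommendation.

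**Conclusion.** The point holds as a gap in ascertainment. Incision infection is named twice as a consequence of wound cracking, yet it has no solicited item and depends on reporting that may under-record it or attribute it differently by arm. The direction and size of any bias are unknown, because no infection rate or recording practice is given. The conclusion assumes that the safety section describes collection as it will be done and that no separate infection item exists in documents not shown.

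A reader might go further and infer that the safety of suturing cannot be tested because of this omission. The documents do not support that. Infections can be recorded and compared as adverse events, and the plan makes no separate safety claim for suturing. The arms differ in instrument, suturing and injection, and there is no unsutured ultrasonic arm. Suturing alone could not be isolated even with a perfect infection item; that limit comes from the comparator.

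This is a cheap improvement to outcome coverage. It affects neither the sample size nor the primary analysis.

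**What to change.** Add incision infection to Secondary outcome measures and Table 1 as a with/without item, with one written criterion applied to both arms. Score it at every inspection that already scores oedema, and record it whatever its judged relation to treatment. Opening of the incision can be added in the same way as an option. If the full protocol or case report form already has such an item, cite it in the article.

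Report counts by arm with exact confidence intervals, as a description of the two operations as packages and not of suturing alone. No confirmatory test is warranted at this size.

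The cost is one or two tick boxes at existing visits and a minor amendment. There are three limits. Patients already enrolled, about two thirds, need a review of their wound notes, reported separately from prospectively scored data. The prospective part would be about 13 per arm at most on the stated recruitment, and fewer if the amendment comes later. A written criterion narrows the scope for unblinded judgement but does not remove it.
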